### Sample size and power

The primary goal of this study is to evaluate the influence of a clinician communication intervention on use of the 5As in communication about physical activity in the post-intervention period (immediately post and at one year) compared to baseline as assessed by audio-recorded data. The sample includes a planned maximum of 15 clinicians (eight in Group 1 and seven in Group 2) measured at three (Group 1) or four (Group 2) time points. The measurements consist of a total of 25 audio-recorded patient visits from each clinician distributed across each of the evaluation points: approximately 10 recordings at baseline and seven or eight each at post- and follow-up points. Of the planned 375 recorded visits, we estimate up to 20% may be excluded from the analysis due to the patient or clinician shutting off the recorder, or equipment malfunction, thus leaving approximately 300 recorded visits (about seven per clinician per time point, or 20 total per clinician) for analysis. Pilot data with 46 recorded visits from eleven physicians showed that the average 5A score was 0.74, with a standard deviation of 1.06. Thus, with 15 clinicians and 20 patients per clinician, we will have 80% power to detect a difference of 0.54 between Groups 1 and 2, using a two-sided t-test at 0.05 significance level.

The final analyses will use a mixed effects model to incorporate correlations between the observations made by the same physician. The variance in 5A scores taken from patients within a single physician's patient panel will likely be smaller than the variance of scores taken from patients between different physicians, i.e. the intraclass correlation coefficient (the ratio of between-physician variance to the sum of between- and within-physician variances) will be larger than zero. We have conducted a series of power analyses taking this clustering into effect using a Mann–Whitney two-sample t-test of means.

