**Figure 1 F1:**
[figure not shown]
Study Schema.

The project is a two-arm randomized pragmatic trial to pilot a communication training intervention for primary care clinicians (n=13) on use of the 5As to promote physical activity in underserved patients. The intention of training focuses on clinicians to communicate effectively using the 5As and patient-centered communication skills firmly linked to a theory of human motivation (Aim 1). Clinicians are randomly assigned to two groups. Group 1 participates in the training intervention first; Group 2 receives the intervention six months later. The primary outcome is the frequency and quality of clinician use of the 5As during routine office visits, post-intervention compared to baseline. Secondary outcomes and potential mediators are changes in patients’ perceived competence to adopt physical activity (Aim 2) and clinician autonomy support of physical activity with their patients (Aim 3). Given the myriad of barriers reported in the literature, another secondary outcome is whether clinicians believe that the intervention addresses pertinent barriers to promoting exercise (Aim 4). Exploratory outcomes are other potential mediators of the intervention’s effect and the effect of the intervention on actual physical activity levels in a subset of participants. The schema shows the overall study design and timeline.

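### The 80% power claimed for a 0.54 difference between Groups 1 and 2 does not follow from the inputs stated, and a one-time-point comparison of the groups falls short of it

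*Protocol article*

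**What the plan says.** All of the power reasoning is in the article's section on sample size and power.

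- Pilot data: "the average 5A score was 0.74, with a standard deviation of 1.06".
- Clinicians: "a planned maximum of 15 clinicians (eight in Group 1 and seven in Group 2").
- Assessments: the clinicians are "measured at three (Group 1) or four (Group 2) time points".
- Visits: 25 planned per clinician, about 10 at baseline and seven or eight at each of the two later points. Up to 20% loss leaves about 300 visits, described as "about seven per clinician per time point, or 20 total per clinician".
- Result: "with 15 clinicians and 20 patients per clinician, we will have 80% power to detect a difference of 0.54 between Groups 1 and 2".
- Test behind the result: it was obtained "using a two-sided t-test at 0.05 significance level".
- Clustering: the next paragraph says that the ICC exceeds zero and that further power analyses were done, "taking this clustering into effect using a Mann–Whitney two-sample t-test of means". It gives neither an ICC nor a result.

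The section on statistical analyses compares mean scores between and within groups at each of three time points, in a mixed model with clinician as a random effect and baseline score as a fixed effect. H1 itself is a post-versus-baseline change. The study design section gives the sample as "primary care clinicians (n=13"), whereas the abstract and the power section use 15.

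**The concern.** The power sentence presents 0.54 as the consequence of the SD, the clinician number, the visits per clinician and the test. A reader who puts those numbers in does not get 0.54.

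The 20 visits are also a total over all time points. They include visits recorded before training, which carry no treatment effect, and Group 2 is trained later, so its later visits are not untrained controls. Twenty visits per clinician are therefore never one trained-versus-untrained sample.

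This is the only quantified power statement in the article. If it is taken at face value, a null difference between Group 1 and Group 2 would be read as good evidence against an effect of 0.54, when that contrast had clearly less than 80% power to show it.

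**Working it through.** **Inputs from the article.** SD 1.06; 8 v 7 clinicians; two-sided alpha 0.05; 20 analysable visits per clinician. Usable visits: 375 × 0.8 = 300; 300/15 = 20; baseline 10 × 0.8 = 8; each later point 7.5 × 0.8 = 6. The article's seven per time point is 20/3 ≈ 6.7, an average that includes the larger baseline.

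**Assumption.** The ICC is not given, so a range is shown. Power and detectable difference (at 80% power) use the noncentral t unless marked z.

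**1. The plan's own figure.** Visits 8 × 20 = 160 and 7 × 20 = 140.
- SE = 1.06 × √(1/160 + 1/140) = 0.123, and 0.54/0.123 = 4.4.
- Power is 99%; the detectable difference is 0.34. The stated 80% is not reproduced.
- An equal split (99%), a one-sided test (over 99%) and Mann–Whitney efficiency (98% to 99%) do not change this.

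**2. What would give 0.54.**
- About 61 to 62 independent visits per group, a number that the article does not contain.
- Twenty visits per clinician with ICC 0.077 (z, design effect 1 + 19 × 0.077 = 2.46, SE = 0.123 × √2.46 = 0.193, 2.80 × 0.193 = 0.54), or ICC 0.058 (t-test on clinician means, 13 df).
- Eight visits per clinician at one time point with no loss and ICC 0 comes close (64 v 56: 79%), but this contradicts the planned 20% loss and the statement that the ICC exceeds zero.

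**3. Group 1 v Group 2 at one post point, unadjusted.** SD of a clinician mean over m visits = 1.06 × √(ICC + (1 − ICC)/m); SE = that SD × √(1/8 + 1/7); 13 df. With m = 6:

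| ICC | SE | Power for 0.54 | Detectable difference |
|---|---|---|---|
| 0 | 0.224 | 61% | 0.68 |
| 0.05 | 0.250 | 52% | 0.76 |
| 0.10 | 0.274 | 45% | 0.83 |
| 0.20 | 0.317 | 35% | 0.96 |

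With the article's own seven visits, all treated as independent (56 v 49), power is 73% and the detectable difference 0.59.

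**4. The same contrast with baseline adjustment.** Assume 8 usable baseline visits and a clinician effect that is stable over time. Residual variance factor = v − ICC²/v₀, with v = ICC + (1 − ICC)/6 and v₀ = ICC + (1 − ICC)/8; 12 df.

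| ICC | Power for 0.54 | Detectable difference |
|---|---|---|
| 0 | 60% | 0.68 |
| 0.10 | 52% | 0.75 |
| 0.20 | 52% | 0.75 |
| 0.40 | 61% | 0.68 |

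**5. H1 as a within-clinician change.** Assume a common effect and a stable clinician effect, with 8 baseline visits and 6 + 6 = 12 post visits. SD of the change = 1.06 × √((1 − ICC)(1/8 + 1/12)); 15 clinicians, 14 df.
- ICC 0: SD 0.484, SE 0.125, power 98%, detectable change 0.38.
- ICC 0.20: SD 0.433, SE 0.112, power 99%, detectable change 0.34.
- One post point only (6 visits): 92% to 97%.

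**6. Thirteen clinicians.** Taking 7 v 6 (an assumption), 6 visits and ICC 0.10, the unadjusted between-group power is 39% and the detectable difference 0.91.

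**The case against.** Four objections deserve weight.

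*Clustering may have been built in.* An ICC of 0.06 to 0.08 at 20 visits recovers 0.54, the article says that clustered analyses were done, and a condensed article may leave the ICC to the full protocol. This stands against any claim that 0.54 is impossible or was wrongly calculated. It does not rescue the sentence, which offers the figure as following from inputs that do not yield it. That route also counts the pre-training visits as outcome visits.

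*H1 is a pre-post change, not a group comparison.* This also stands. A reader might infer that the trial as a whole had even odds or less of detecting 0.54. The documents do not support that: step 5 gives over 90% for the change pooled over 15 clinicians. But the power sentence names Groups 1 and 2, and the analysis section plans that comparison, so the shortfall there remains.

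*The planned model adjusts for baseline.* This stands and removes the low end of the unadjusted range, 35% power and 0.96. It does not reach 80% at any ICC from 0 to 0.4.

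*A two-sample test on clinician means does allow for clustering.* Correct. A reader might infer from the Mann–Whitney wording that clustering was ignored. The text shows only that a rank test and a test of means are run together under one name.

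The 13 against 15 discrepancy does not show that the arithmetic is wrong either, since 15 is called a planned maximum. It leaves the basis of the calculation unclear.

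**Conclusion.** The concern holds for the figure as printed and for the contrast it names. On the stated inputs, power for 0.54 is about 99% and the detectable difference about 0.34. To reach 80% at 0.54, a reader must supply an ICC of about 0.06 to 0.08 and count about 8 pre-training visits per clinician as outcomes.

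For Group 1 v Group 2 at one post time point, with about 6 usable visits and 8 v 7 clinicians, power for 0.54 is about 35% to 61% unadjusted (ICC 0.20 to 0). With baseline adjustment it is about 52% to 61%, assuming 8 baseline visits, a stable clinician effect and ICC 0 to 0.4. The article's own seven visits per time point give at best 73%, with every visit treated as independent.

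The shortfall does not extend to the pooled within-clinician change in H1, provided that the effect is common to both groups and clinician effects are stable.

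Two features could lower the between-group figures further. Group 2's visits may be spread over four time points, and H1 counts only visits in which physical activity comes up. The article gives no split or share from which to size either effect.

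**What to change.** Rewrite the power paragraph so that it can be reproduced:

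- Name the contrast and the time point, the usable visits per clinician at that point, the ICC or an ICC range, and whether baseline is adjusted for.
- Restate the detectable difference for Group 1 v Group 2 at one time point. On the article's figures this is about 0.7 to 0.75 baseline-adjusted (ICC 0 to 0.4) or about 0.7 to 1.0 unadjusted (ICC 0 to 0.20).
- Give the within-clinician figure for H1 separately, with its assumptions.
- Replace the Mann–Whitney sentence with the cluster-level method actually used, and give its result.
- Base the calculation on one clinician number, 15 or 13, and use it throughout.

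The cost is text only: a less favourable between-group figure, with no extra clinicians or visits and no change to the planned model.

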### Process evaluation

Process evaluation data will be analyzed to examine the feasibility and acceptability of the intervention. Qualitative data consist of field notes of all clinician training sessions, observation notes on recruitment procedures and cooperation between clinical and research staff, correspondence notes and meeting minutes between community partners and study staff, notes from study staff and faculty research meetings, patient post-study interviews and focus groups, and transcribed clinician interviews. A multidisciplinary team will conduct the qualitative analysis using grounded theory, [63,64] a coding-editing approach, in two phases. In the first phase, members of the team (undergraduate students) will systematically code all qualitative data and meet regularly with the principal investigator, who has expertise in qualitative research, to review codes, identify and resolve discrepancies, and discuss emerging concepts. For the second phase, a multidisciplinary group of faculty and graduate-level trainees will review the codes and concepts to develop the key themes related to the intervention’s feasibility and acceptability. Quantitative process measures consist of clinician attendance at all training sessions, clinician fidelity to the intervention (measured by audio recordings), other clinic staff participation in patient recruitment, patient participation rate, reasons for patient refusal or ineligibility, patient completion of all study measures, patient follow-through at the community program referral and pre-post clinician ratings of usefulness or recommendation of the community resources to their patients.

### Assessing cross-contamination

We will use the audio-recorded data to measure cross-contamination in Group 2 clinicians to evaluate the extent to which they could be influenced by the intervention. Specifically, we will assess changes in Group 2’s 5A scores from two baseline measurements at months 1–3 and months 12–15. Trained research staff, blinded to the clinician’s group assignment, will listen to the baseline audio-recorded sessions of Group 2 clinicians and use pre-developed intervention adherence checklists to evaluate whether Group 2 clinicians incorporated specific intervention-related materials into their visits and whether they explicitly used the 5As or patient-centered communication constructs in their visits. Group 2 clinicians will also be asked directly in their post-study individual interviews whether they were aware of the study activities from Group 1 and the extent to which it influenced their counseling, if applicable.

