### Recruitment of clinician participants

The principal investigator presents an overview of the study’s objectives, design, and time frame to eligible clinicians at a weekly clinician meeting. Each clinician’s full participation requires the clinician to 1) complete a 10 minute written baseline assessment, 2) attend four one-hour training sessions held during regularly scheduled provider meeting times over a four-month period, 3) consent to having 10 patient visits audio-recorded at baseline and 15 at post-intervention, and 4) complete a post-intervention survey and a 20 minute individual interview. Based on estimates from a previous pilot project, we anticipate a 10 patient visits at baseline should be sufficient; however, if the visits do not contain any discussions of physical activity, clinicians are told that the baseline assessment may consist of > 10 visits. In addition to clinicians’ informed consent, research staff explain that patient informed consent is obtained prior to any recording. For patients providing informed consent, an audio-recorder is placed unobtrusively in the exam room. Each clinician receives $60 per completed hour of the four hours of training and $5 per recorded visit. The principal investigator also explains the overall goals and procedures of the study to all clinical staff at their regularly scheduled team meetings. Staff are encouraged to forward any inquiries from patients about the study to members of the study team. The clinical practice receives a $2000 stipend for use of the facility and staff time. Clinician participants then provide written informed consent.

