### Patient post-visit survey

After the recorded visit, a brief face-to-face survey is administered to the patient participants. Items include socio-demographics data (age, gender, marital status, race and ethnicity, highest educational level attained, and insurance status), the SF-12, and other measures described in (sections Evaluation and measures and Exploratory outcome measures). The survey takes about 15 minutes. Patients then complete a 5–10 minute interview asking about their perspective on the content, adequacy, and clarity of communication about physical activity counseling.

Patients are compensated a total of $20 ($10 for participating in the audio recording portion and $10 for their time completing the survey and interview).

After the baseline assessment is completed for Group 1 clinicians and their corresponding patients, Group 1’s training intervention begins.

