### Post-intervention clinician assessment

The post-intervention clinician assessment occurs immediately upon completion of the intervention (or at approximately 6 months from the baseline assessment) and 6 months follow-up (or 12 months from the baseline) in the same manner described previously. Clinicians complete post-intervention and follow-up assessments of 15 audio-recorded office visits, divided across the two time points in the same manner as described in section 2.8. Group 1 clinicians complete a survey asking about the feasibility of the intervention, and individual brief interviews are conducted.

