### Group 2 (wait-list)

The clinician baseline assessment for Group 2 is identical to that for Group 1. The Group 2 assessment occurs at 0–3 months (concomitant with the Group 1 clinician baseline) and again at 9–12 months (concomitant with the Group 1 post-intervention assessment.)

Group 2’s clinician training intervention occurs in the same manner as described in the section, Description of Intervention (section 2.11) for Group 1. Standardization of both Group 1 and Group 2’s training intervention sessions is assessed by audio-recording all sessions and ensuring that the key objectives of each session are met using a pre-developed checklist and via rating by a trained research staff member not involved in delivering the intervention.

Group 2’s Post-Intervention Assessment occurs immediately post-intervention and at six months post-intervention in the same manner as described previously for Group 1 (section Post-Intervention Clinician Assessment). As with Group 1, Group 2 clinicians also complete a survey asking about the feasibility of the intervention and individual exit interviews.

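### Group 2's second pre-training assessment, the only untreated data concurrent with Group 1's post-training visits, carries two conflicting dates, and the printed recording allocation fits only three of Group 2's four time points

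*Protocol article*

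**What the plan says.** All references are to the protocol article.

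- **Second Group 2 assessment, first statement.** Group 2 (wait-list): "The Group 2 assessment occurs at 0–3 months (concomitant with the Group 1 clinician baseline) and again at 9–12 months". The sentence goes on to call the later window concomitant with Group 1's post-intervention assessment.
- **Second Group 2 assessment, second statement.** Assessing cross-contamination: change in Group 2's 5A score is to be read from "two baseline measurements at months 1–3 and months 12–15".
- **Group 1's post-training assessments.** Post-intervention clinician assessment: "immediately upon completion of the intervention (or at approximately 6 months from the baseline assessment) and 6 months follow-up (or 12 months from the baseline".
- **Order and lag of training.** Study design: "Group 1 participates in the training intervention first; Group 2 receives the intervention six months later". Patient post-visit survey: "After the baseline assessment is completed for Group 1 clinicians and their corresponding patients, Group 1’s training intervention begins". Recruitment of clinician participants: each clinician must "attend four one-hour training sessions held during regularly scheduled provider meeting times over a four-month period".
- **Recordings.** Sample size and power gives Group 1 three time points and Group 2 four, and allots 25 recordings to every clinician as "approximately 10 recordings at baseline and seven or eight each at post- and follow-up points". After a 20% loss it expects 20 usable visits per clinician, about seven at each time point. The consent terms for clinicians repeat the split as 10 at baseline and 15 afterwards.
- **Model.** Statistical analyses names three time points: baseline, immediately post-intervention and follow-up.

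**The concern.** In a wait-list design, the early group's post-training data need data from the late group that are recorded at the same time and before the late group is trained. Here that is Group 2's second assessment. The first baselines of both groups are also untreated, but they precede Group 1's training. They cannot separate a training effect from a calendar trend or from the effect of being recorded, which the Design limitations section says the two-group design will help to assess.

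Two things are at stake. If the second assessment is recorded during or after Group 2's own training, the change between Group 2's two baselines contains the training effect, and the cross-contamination analysis would report it as contamination. Any concurrent contrast between groups would also compare trained clinicians with partly trained ones and be pulled towards zero. If instead the assessment is not concurrent with Group 1's post-training data, calendar time is mixed with the effect.

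The allocation of recordings adds to this. The time point that the contrast needs has no line of its own in the printed split.

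**Working it through.** **1. The two dates.** Months 9–12 and months 12–15 share only the boundary at month 12. Both statements are current text.

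**2. Where Group 2's training falls.** Inputs: baseline in months 0–3, Group 1 training starting at month *s* after baseline, training lasting 4 months, and a lag of 6 months. The value of *s* and the point from which the lag runs are not printed, so both are varied. Group 2 trains from *s* + 6 to *s* + 10 if the lag runs from Group 1's start, from *s* + 10 to *s* + 14 if it runs from Group 1's end, and from month 6 to month 10 if it runs from month 0.

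| Lag counted from | *s* | Group 2 trains (months) | Overlap with 9–12 (months) | Overlap with 12–15 (months) |
|---|---|---|---|---|
| Group 1 start | 3 | 9–13 | 3 | 1 |
| Group 1 start | 4 | 10–14 | 2 | 2 |
| Group 1 start | 5 | 11–15 | 1 | 3 |
| Group 1 start | 6 | 12–16 | 0 | 3 |
| Group 1 end | 3 | 13–17 | 0 | 2 |
| Group 1 end | 4 | 14–18 | 0 | 1 |
| Group 1 end | 5 | 15–19 | 0 | 0 |
| Group 1 end | 6 | 16–20 | 0 | 0 |
| Month 0 | – | 6–10 | 1 | 0, but wholly after training |

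In seven of these nine readings at least one window lies partly or wholly during or after training: 9–12 in four, 12–15 in seven. Both are clear only when the lag runs from the end of a Group 1 training begun at month 5 or later. The readings are not equally likely, so the counts are not probabilities.

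**3. Concurrency with Group 1.** Six months from a baseline in months 0–3 is months 6–9; counted from the end of baseline it is month 9, where the 9–12 window opens. Training that starts at month 3 ends at month 3 + 4 = 7. Twelve months from baseline is months 12–15, which is Group 1's follow-up and not its immediate post assessment. So 9–12 can match the immediate post assessment on some readings, but 9–12 and 12–15 cannot both do so.

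**4. Recording budget.** The plan's totals reproduce: 15 × 25 = 375; 375 × 0.8 = 300; 300 / 15 = 20 per clinician. The split is 10 + 7.5 + 7.5 = 25, which uses everything on three points, and 20 / 3 = 6.7 matches the stated seven. For Group 2's four points, 25 / 4 = 6.25 planned and 20 / 4 = 5 usable. Over the whole trial there are 8 × 3 + 7 × 4 = 52 clinician-time-points; at seven each they need 364 usable visits, against about 300.

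**5. Effect on the detectable difference.** Inputs: SD 1.06, 8 and 7 clinicians, 80% power and two-sided 0.05 (Sample size and power); ICC 0.05–0.10 is an assumption. For one time point, analysed on clinician means with 13 degrees of freedom:

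MDD = (2.160 + 0.870) × 1.06 × √{[ICC + (1 − ICC)/m₁]/8 + [ICC + (1 − ICC)/m₂]/7}

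| ICC | 7 vs 7 visits | 7 vs 5 visits |
|---|---|---|
| 0.05 | 3.03 × 1.06 × √(0.1857/8 + 0.1857/7) = 0.72 | 3.03 × 1.06 × √(0.1857/8 + 0.2400/7) = 0.77 |
| 0.10 | 3.03 × 1.06 × √(0.2286/8 + 0.2286/7) = 0.80 (0.795) | 3.03 × 1.06 × √(0.2286/8 + 0.2800/7) = 0.84 |

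The plan's 0.54 is on another footing. Without clustering, 2.802 × 1.06 × √(1/160 + 1/140) = 0.34 for all 300 visits, and 64 against 56 visits gives 0.54. The figures to compare here are therefore 7 vs 7 and 7 vs 5, which differ by about 0.05.

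**The case against.** The strongest reply is that the overlap is inferred. No start date for Group 2's training is printed, and the length of baseline is left open, because clinicians may be asked for more than 10 visits and patients are recruited until the baseline information is adequate. If Group 1 trains in months 5–9, its immediate post assessment falls in months 9–12, as the wait-list section says. If the six months then run from month 9, Group 2 starts at month 15 and both windows are clean. This stands. A reader might infer that the second assessment necessarily falls within Group 2's training, or that neither window can match Group 1's immediate post assessment; the text supports neither. It supports only that the printed dates permit such an overlap on most readings and that nothing in the text rules it out.

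Three further limits also stand.

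- A reader might call this assessment the only untreated comparator. It is not: Statistical analyses also uses the first baselines of both groups. It is the only untreated comparator concurrent with Group 1's post-training data.
- The primary model does not say how this assessment enters. Its one stated use is the contamination check, so dilution of the between-group contrast depends on its being used there.
- A reader might infer that Group 2's second assessment has no recordings at all. The text says that recordings are spread over each evaluation point and that the split is approximate, so the allocation is unclear, not demonstrably zero.

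The schema figure is not available here and may carry a calendar. It could show which date is intended, but it would not make the two printed windows agree.

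**Conclusion.** Two defects hold on the text alone. The second Group 2 assessment has two incompatible dates, and the 25-recording split and the figure of seven visits per time point fit three points, whereas Group 2 has four.

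The overlap with Group 2's training is conditional. On the plain reading (Group 1 starts at month 3, lag counted from that start) it covers all of months 9–12 and one month of 12–15. It disappears for both windows only if the lag runs from the end of a Group 1 training begun at month 5 or later.

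The cost of the thinner allocation is modest: about 0.05 on the detectable difference (0.72–0.80 rising to 0.77–0.84), resting on the assumed ICCs and a single-time-point analysis of clinician means. A reader might go further and say that a true difference of 0.54 would be halved to 0.27. That holds only if Group 2 already showed half the effect, and no figure in the plan supports such a fraction.

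The point still needs correcting before the analysis. A baseline recorded on the printed dates can be a trained measurement, and this would spoil both the contamination check and any concurrent control.

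**What to change.** 1. Reconcile Study design, Post-intervention clinician assessment, Group 2 (wait-list), Sample size and power, and Assessing cross-contamination into one calendar that gives a start and an end for each group's training and each assessment.
2. State that Group 2's second recordings share Group 1's immediate-post window and close before Group 2's first training session. Do not count any recording made after that session as baseline.
3. Print a four-point allocation for Group 2, about 6 planned and 5 usable visits per point, and correct the figure of about seven per time point for that group.

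The first two changes cost only wording. The third stays within 375 recordings, but Group 2 has fewer visits at its other points. Reserving seven planned recordings for the extra point would not give seven usable ones: 7 × 0.8 = 5.6. Keeping 7–10 planned there without cutting the other points needs 7 × 7 = 49 to 7 × 10 = 70 more recordings, for a total of 424–445.
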